#### Analysis of secondary outcomes

For the type of vascular access used at start of RRT, analysis will be conducted in the same way as the analysis of primary outcome (mixed-effect logistic regression of the binary outcome 0/1, where 0 = permanent access and 1 = temporary access). This analysis will be performed on all new patients starting RRT with any treatment modality and also restricting the cohort to patients starting RRT on haemodialysis.

Latest eGFR measurement preceding RRT start in new RRT patients will be analysed using a mixed-effects linear regression model. Transformation of the response variable ‘eGFR’ may be necessary to achieve a normal distribution prior to analysis. The same model building sequence will be used as for the logistic analysis of the primary outcome.

The analysis of the six months mortality in new RRT patients will be conducted in the same way as the analysis of the primary outcome, using a mixed-effect logistic model (binary outcome, 0 = alive after 6 months from start of RRT, 1 = died in the 6 months following start of RRT).

The incidence rate of RRT (expressed as number of patients starting RRT per million population), will be analysed using Poisson regression. This will be a cluster-level analysis, with one measure per time-period per renal centre.

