### Project design

It is planned that the eGFR graph intervention will be implemented in laboratories serving at least nineteen renal centres across the UK. All sites participating in this quality improvement programme will receive the intervention. However implementation will proceed in a phased stepped wedge manner (“stepped wedge cluster randomised trial”) to allow a robust outcome evaluation to be conducted. Without this design, evaluation of the overall project success may be overly optimistic due to the phenomenon of “early-adopters”.

The unit of intervention in the project is the pathology laboratory. However project outcome measures are aggregated at the level of the renal centre. Where more than one laboratory lies within the catchment of a main renal centre, where possible the intervention will be implemented in all these laboratories simultaneously.

The intervention will be rolled-out sequentially, with renal centre clusters (and their associated pathology laboratories) receiving the intervention at staggered time points. The plan is for four or five renal centres to begin implementation at each “step”, with a six-month interval between steps. The time of intervention initiation will be randomised. Crossover is unidirectional (from control to intervention) so eventually all participating centres will implement the intervention, see Table 1 for a representation of the step-wedge process.

**Table 1 Tab1:** Study period with randomisation steps

Centres	Historical control-periods				Periods of core-study					
	(4 × 6 months)				Jan-Jun	Jul-Dec	Jan-Jun	Jul-Dec	Jan-Jun	Jul-Dec
	Jan-2013 - Dec 2014				2015	2015	2016	2016	2017	2017
A – D	0	0	0	0	0	1	1	1	1	1
E – I	0	0	0	0	0	0	1	1	1	1
J – N	0	0	0	0	0	0	0	1	1	1
O – R	0	0	0	0	0	0	0	0	1	1

0=’control’; 1=’intervention’ - eGFR graph surveilence

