### Outcome measures

Outcomes will be examined at renal centre level and, if necessary, laboratory level using Geographic Information Systems to map patients to laboratories. Routinely collected baseline data will be provided by the UK Renal Registry and baseline referral rates supplied by participating centres.

The UK Renal Registry (UKRR) routinely collects and publishes treatment and clinical performance data for all adult renal centres in the UK [10]. As part of this, it routinely receives an extract of data on numbers of patients starting dialysis in each renal centre and timeliness of referral.

Our primary quantitative outcome measure is the incidence of late presentation for renal replacement therapy, defined as any patient first seen by renal services within 90 days of starting renal replacement therapy. These data will aggregate into six-month time periods, two per calendar year (Jan to June; July to December).

The following secondary outcomes will be studied:(i.)the use of temporary vascular access for starting dialysis(ii.)latest eGFR measurement, within two weeks before start of RRT(iii.)mortality at 6 months from start of RRT in new RRT patients(iv.)the incident rate of ESKD, measured annually.

All outcomes measures are routinely collected by the UK Renal Registry with the exception of vascular access, which is collected annually as part of the Registry’s Multisite Dialysis Access Audit.

The number of new patient referrals (per quarter) will be recorded as a balancing measure. These data are readily extractable from renal centre appointment systems.

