#### Analysis of primary outcome

Analysis of changes in risk of late-referral will be performed using a mixed-effects logistic regression, as a patient level analysis, with the clustering at renal centres being accounted for by fitting renal centre as a random effect. The primary outcome response will be binary (patient referral <90 days = 1, patient referral ≥90 days = 0). It is expected that the risk of being late referred should decrease with the intervention. The odds ratio estimate of the risk of being late-referred for the treatment effect (intervention versus control) with 95% confidence interval will be presented (model 1). Analysis will be adjusted by time-period or step (model 2), and individual patients’ characteristics such as age at start of RRT, gender, primary renal diagnosis, ethnicity and deprivation score (model 3). Due to the nature of the intervention it is anticipated that its impact on late referral will change over time, as the risk of being late-referred is expected to decrease after the intervention is implemented, and possibly more so with time from start of intervention (we expect a cumulative effect, at least up to a certain point). Therefore we aim to explore for possible interaction between time and treatment effect (model 4).

The results from model 2 will be considered the primary result, as our intention is to determine if changes in the risk of being late-referred for RRT are related to the intervention and not to an independent time-trend.

Power calculations for the primary outcome have been derived on Stata [11], based on UKRR data returns from twelve candidate renal centres. The UKRR reached complete coverage of the UK in 2007 and data on adult incident RRT patients have been routinely collected since then. Therefore we are able to use data on new incident patients commencing RRT before the project started, and we plan to include in the analysis the population of RRT incident patients in 2013–14 for the participating centres. We therefore used the formula published by Woertman, which can accommodate the inclusion of additional historic data [12]. The percentage of late referral in these twelve centres ranged from 9 to 35%, with an average of 18%. With power set at 80%, alpha at 0.05 and intra-class correlation (ICC) at 0.05 (based on analysis of UKRR 2013 data) we should be able to detect a reduction in late presentation rate from 18 to 11%.

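### RRT incidence is given a Poisson model with no stated allowance for repeated records from the same centres, and its measurement interval is annual in one section and per time-period in another

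*Protocol article*

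**What the plan says.** Under Analysis of secondary outcomes, the article states the outcome as "The incidence rate of RRT (expressed as number of patients starting RRT per million population" and says that it "will be analysed using Poisson regression. This will be a cluster-level analysis, with one measure per time-period per renal centre". Nothing further is said about the model, and this outcome is not tied to the model sequence of the primary outcome.

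The other outcomes are handled differently:

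- Primary outcome: a mixed-effects logistic model, "with the clustering at renal centres being accounted for by fitting renal centre as a random effect".
- Vascular access: analysed in the same way as the primary outcome.
- Last eGFR before RRT: "will be analysed using a mixed-effects linear regression model", with the primary outcome's model sequence.
- Six-month mortality: analysed as the primary outcome, "using a mixed-effect logistic model (binary outcome, 0 = alive after 6 months from start of RRT".

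On the interval, Outcome measures lists "the incident rate of ESKD, measured annually". I take this to be the same outcome as the RRT incidence rate, since it is the fourth of four secondary outcomes and no other analysis is given for it. The only period length in that section is stated for the primary outcome: "These data will aggregate into six-month time periods, two per calendar year (Jan to June; July to December". Under Project design, centres start in groups "with a six-month interval between steps", and Table 1 sets out four historical and six core half-year periods.

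**The concern.** Aggregating to centre level does not remove clustering in a stepped wedge, because each centre still supplies a series of counts (ten on the Table 1 layout). A Poisson model with no centre term assumes that these counts differ only by chance around a common rate. Any stable difference in incidence between centres then enters the comparison as variation that the model does not recognise, and the reported standard error is too small. The intervention could appear to raise or lower RRT incidence when it does neither.

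The interval matters because half of the steps fall in July. A calendar-year record for a centre that switches in July is part control and part intervention.

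A falling RRT incidence is part of the evidence from the originating Trust (Abstract and Background), and avoided dialysis is the argument of the local business case (Support for participating sites). A falsely precise result on this outcome could therefore be taken seriously by commissioners.

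**Working it through.** **Plan's own figure.** There is none for this outcome. The only design calculation (80% power, 18% to 11% late presentation, ICC 0.05) concerns the primary outcome and does not bear on this point.

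**Inputs from the article.** Table 1 has 18 centres and 4 + 6 = 10 six-month periods. Groups A–D (4 centres) switch in July 2015, E–I (5) in January 2016, J–N (5) in July 2016 and O–R (4) in January 2017. The text elsewhere gives at least 19 centres.

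**Inputs assumed, because the article gives neither.** RRT starts per centre-period: 25, 50 or 75. Between-centre coefficient of variation (CV) of the underlying rate: 0 to 0.3.

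**Step 1: effect of leaving out the centre term.** Data were simulated on the Table 1 layout with six-month records (18 × 10 = 180) and no true intervention effect, 800 runs per setting. Two Poisson models were fitted, both with an intervention term and period effects: one without centre effects, one with fixed centre effects. Ratio = true SE / mean SE reported by the model; type I error = share of runs with |estimate / SE| > 1.96.

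| Starts | CV | Model SE | True SE | Ratio | Type I, no centre effect | Type I, centre effects |
|---|---|---|---|---|---|---|
| 25 | 0.1 | 0.0611 | 0.0730 | 1.19 | 10.0% | 4.8% |
| 25 | 0.2 | 0.0611 | 0.1091 | 1.78 | 26.2% | 5.9% |
| 25 | 0.3 | 0.0613 | 0.1445 | 2.36 | 42.9% | 4.0% |
| 50 | 0 | 0.0432 | 0.0445 | 1.03 | 5.6% | 6.5% |
| 50 | 0.1 | 0.0432 | 0.0627 | 1.45 | 18.5% | 5.9% |
| 50 | 0.2 | 0.0433 | 0.0971 | 2.24 | 40.4% | 5.9% |
| 50 | 0.3 | 0.0433 | 0.1360 | 3.14 | 53.6% | 5.5% |
| 75 | 0.1 | 0.0353 | 0.0553 | 1.57 | 21.6% | 4.6% |
| 75 | 0.2 | 0.0352 | 0.0891 | 2.53 | 45.8% | 5.9% |
| 75 | 0.3 | 0.0354 | 0.1315 | 3.71 | 59.9% | 5.9% |

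Simulation error at a true 5% is √(0.05 × 0.95 / 800) = 0.8 percentage points, so the last column is compatible with 5%.

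At 50 starts and CV 0.2, the reported half-width on the log scale is 1.96 × 0.0433 = 0.085, where 1.96 × 0.0971 = 0.190 would be needed.

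If the period effects are dropped too (the article does not state them for this outcome), the ratio over the same CVs is 1.10 to 2.03 and the type I error 7% to 36%.

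**Step 2: is a centre effect enough?** With extra centre-by-period variation of CV 0.1 (50 starts, centre CV 0.2), the model with centre effects has a type I error of 8.9%. It is much better than the 38.4% without them, but still above 5%.

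**Step 3: annual or six-monthly.** With six-month records every record is wholly control or wholly intervention, so 0 are half-exposed. With annual records there are 18 × 5 = 90, and the July switchers give 4 (2015) + 5 (2016) = 9 half-exposed records. Fitting a period-adjusted Poisson model to expected annual counts under a true rate ratio of 0.80 gives:

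- half-exposed years coded control: 0.85 without and 0.86 with centre effects;
- coded intervention: 0.87 either way;
- coded 0.5: 0.80.

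All-or-nothing coding would thus shrink a 20% reduction to about 13% to 15%.

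**The case against.** The strongest reply is that the charge rests on silence. Two sentences in a condensed article also leave out the intervention term, period adjustment, offset and variance estimator, and nobody would conclude that there is no intervention term. A centre term could sit in a full analysis plan that is not shown. This stands to the extent that the text does not rule out a centre term. It does not dispose of the point: the article names a model type for every outcome, and this is the only one where that type is not mixed-effects or tied to the primary analysis.

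Several stronger readings are tempting, and the documents do not support them:

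- **That the intervals are far too narrow.** The article gives neither counts nor between-centre variation in incidence. The direction follows from the model; the size rests on assumed values.
- **That nine centres will have a half-exposed year.** This holds only if the annual statement governs. Under the analysis section with six-month periods none do, and the simulation in Step 1 uses six-month data, so the two consequences do not add together. The nine also comes from the 18 centres of Table 1; with 19 it could be nine or ten.
- **That a centre effect alone restores the 5% level.** Step 2 shows that it may not.
- **That the trial's main conclusion or its economic case is at risk.** The primary result comes from a model with a random centre effect and time adjustment. The Economic evaluation section does not say that it will use this incidence estimate.

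The six-month period is also defined only for the primary outcome, so a reader could take a different period to apply here. That leaves the interval for incidence unsettled; it does not reconcile the two sections.

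**Conclusion.** The point holds as two defects in the specification of one secondary outcome.

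First, the named analysis, followed literally, treats repeated counts from the same centres as independent and understates the uncertainty. With period adjustment the understatement is about 1.2-fold to 3.7-fold in the standard error, and the type I error about 10% to 60%. This is conditional on between-centre CVs of 0.1 to 0.3, 25 to 75 starts per centre-period and no centre term being added elsewhere. At a CV of 0 there is nothing to correct.

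Second, the measurement interval is inconsistent between Outcome measures and Analysis of secondary outcomes, if a time-period has the only length that the article defines. This does not depend on any assumed figure. Its consequence, nine centre-years of mixed exposure with no coding rule, arises only if annual data are used.

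Both should be corrected. Neither affects the primary analysis.

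**What to change.** In Outcome measures, replace the annual interval with six-monthly counts of RRT starts, using the same January–June and July–December periods as the steps.

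In Analysis of secondary outcomes, specify a Poisson or negative binomial model for the count, with:

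- log catchment population as offset;
- the intervention term;
- fixed period effects;
- a centre effect;
- an allowance for centre-by-period overdispersion: the negative binomial form, a centre-by-period random effect, or cluster-robust errors with a small-sample correction, since there are only 18 or 19 centres.

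The cost is a few sentences of analysis wording and wider reported intervals. At 50 starts and CV 0.2 the reported standard error rises from 0.0433 to 0.0481 with fixed centre effects (0.0481 / 0.0433 = 1.11), before any overdispersion allowance. In the same setting the true standard error falls from 0.0971 to 0.0484, because stable centre differences no longer enter the comparison.

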### Qualitative evaluation

The aim of the qualitative evaluation is to understand the experiences of those directly involved in the intervention, including laboratory staff, primary care staff, clinicians in renal centres and patients. In addition, the experiences of commissioners in facilitating and monitoring the intervention will be sought. The qualitative evaluation plan is based on previous learning from feedback at the Heart of England Foundation Trust (HEFT) in October 2014.

#### Laboratory staff

One-to-one semi-structured interviews lasting 20–30 min will be conducted with 1–2 laboratory staff in each Trust, either face-to-face or by telephone. Questions will explore the experiences of being involved with the eGFR project, and will include discussion of: what specifically has worked/not worked; how far the training has equipped staff to undertake this new role; and potential recommendations for other labs who will be developing the system in the future. Data will be analysed using simple thematic analysis.

#### Primary care staff

We will conduct an electronic survey, via SurveyMonkey, of a sample GPs who have been sent an eGFR graph. The overall aim of the survey is to determine if the intervention is effective and how far it might impact on a patient’s clinical care. Questions asking about timeliness, usefulness and ease of interpretation will be answered on a Likert scale. Open questions asking about possible impact on patient care and recommendations for future enhancements to the eGFR system will be answered in free text. Quantitative data will be analysed using simple descriptive statistics; free text will be analysed by simple thematic analysis.

One GP surgery in each stage of the intervention roll-out will be approached for an in-depth evaluation. This will involve a focus group with a variety of staff in the practice (GPs, nurse practitioners, practice nurses, practice managers) who may be involved with the intervention. Questions will be open and will commence with ‘What is your experience of using the eGFR system in this practice?’, but will move to further questions around timeliness, usefulness and patient experience. Focus groups will be recorded, data transcribed and analysed using simple thematic analysis.

#### Renal centre staff

Short face-to-face or telephone interviews will be requested and conducted with one nephrologist and one other staff member (eg. clinical nurse specialist or nurse consultant) who are involved in seeing patients who have been referred following GP review of the eGFR graph. Questions will focus on practicalities, such as barriers and enablers of adoption, and sustainability within the renal centre. Notes of the interviews will be taken and common themes identified.

#### Commissioners

Telephone interviews will be conducted with one CCG commissioner or quality improvement lead in each Clinical Commissioning Group (CCG)/Strategic Clinical Network (SCN). Interview questions will focus on impressions about barriers and enablers to adoption across the CCG/SCN, cost-effectiveness, sustainability and spread.

### Economic evaluation

The cost of implementing the intervention will be estimated from the study and existing published costs retrieved for renal outpatient attendances and renal replacement therapy options. Utility index values will be identified from the literature for the various health states possible and used to estimate cost per quality adjusted life year gained from the intervention. A NHS health care perspective will be adopted.

### Patient and public involvement

We have convened a Patient Project Team (PPT), following a successful model developed by members of the project team in a previous quality improvement project [13]. The PPT chair is an integral member of the Core Operational Team, providing patient leadership and contributing on an entirely equal footing to healthcare professionals. Terms of Reference and role descriptions were drawn up and signed off by team members. Members of the group will be reimbursed in accordance with National Institute for Health Research Guidelines [14]. The PPT will: guide and influence the development and delivery of all patient-facing materials within the project; work locally and nationally to facilitate adoption, spread and sustainability, using the power of the patient and carer voice to influence the commissioning process; work closely with healthcare professionals in the design and delivery of the project evaluation; and represent the patient and carer voice at national or local meetings.

### Project oversight

An Advisory and Dissemination Board (ADB) has been established to provide directional stewardship to achieve spread and scale. The role of the ABD will be critical for dissemination and in linking the project to policy change. In addition, an Evaluation Advisory Group will oversee the project evaluation, ensuring that quantitative and qualitative elements are brought together to provide advice on risk/change management.

The project has been registered with the International Standard Randomised Controlled Trials Number (ISRCTN) Registry, registration number 13701669.

### Authorship

Those playing a major role in the design, conduct and evaluation of the intervention will be eligible for authorship of subsequent publications. These will be written by the research group and we will not use professional writers.

## Discussion

Guidelines on the identification and management of CKD that include referral criteria for primary care were issued by the National Institute for Health and Care Excellence in 2008 and revised in 2014 [15]. However cross-sectional data indicate that people with earlier but progressive disease are frequently not recognised and referred by primary care, and that many patients with more advanced but stable disease continue to attend hospital clinics where ongoing specialist input may result in little added value [16].

This suggests that there are significant opportunities for better interaction and integration between primary and secondary healthcare services in the UK to improve the quality and efficiency of kidney care. Late referral for renal replacement from primary care is an important cause of morbidity and mortality amenable to healthcare. Following the introduction of eGFR reporting and the inclusion of CKD within the UK pay-for-performance scheme for general practice there has been a steady decline in the proportion of patients presenting late for RRT, from 26–30% during 2000–2005 [17] to 18% in 2014 [6]. However the highest performing UK renal centres, which include the site at which the eGFR graph intervention was developed and tested, achieve late presentation rates of less than 10% [6]. Therefore evaluating the spread of the eGFR intervention to other centres is an appropriate focus for improvement activities.

Local evidence suggests that the graphical surveillance of kidney function is associated with measurable improvements in care [7, 8]. This project is applying a stepped wedge approach to the dissemination of the eGFR graph intervention, in order to scale up these improvements and to determine the effectiveness of the intervention away from the environment in which it was developed. The critical role of context in improvement work is well-described [18]. A stepped wedge design is particularly appropriate for the evaluation of interventions during routine implementation [19], and will complement the concurrent roll-out of the eGFR graph intervention across the West Midlands that is being funded by NHS England via the West Midlands Strategic Clinical Network and Clinical Senate [20].

Our statistical model balances the competing effects on power of the number of steps and the length of time between steps [21]. The quantitative analysis will be strengthened by the availability of a minimum of 2.5 years of high quality routinely collected baseline data at all sites, and supported by a qualitative element that will explore the barriers and enablers of change and the perceptions of the participants as described above.

The role of ethical oversight of quality improvement projects has been the subject of heated debate over recent years [22]. Recent reviews have emphasised a principle-based rather than a rule-based approach to determine whether an activity requires formal ethical approval, with the key elements including: the risks and benefits to existing or future patients; the need to respect individuals’ rights to self-determination; the preservation of privacy and confidentiality; and the distribution of the activity across patient groups [23]. The project team carefully considered these issues internally. It was recognised that the risks and burdens to patients were minimal. The project uses existing biochemical data within the laboratory and outcome measures are routinely collected. There is no allocation to different interventions across patient groups: due to the stepped-wedge design all participants receive the intervention by the end of the project. However, we also recognised that the project evaluation would generate new knowledge potentially relevant to the health service more widely. Accordingly we sought external advice, from both a former ethics chair and an independent expert. Their opinion was that the project appeared not to meet the criteria for research, but that a formal opinion from an Ethics Committee would be helpful. We therefore presented the project to the National Research Ethics Service for consideration (South East Coast-Surrey Committee): the Chair’s opinion was that the project was a service improvement/evaluation and did not require ethical approval.

Given the extreme financial constraints under which the UK National Health Service is currently operating, it is imperative to perform a robust evaluation of any quality improvement intervention. The proposed evaluation will ensure that the project is delivering improvement as expected and therefore represents an appropriate use of scant resource. It will also help to inform the aformentioned sites where the eGFR graph intervention is being introduced routinely outside the project [20].

The project has limitations and challenges. We recognise the complexities inherent in a stepped wedge approach, from both an analytical and operational perspective. The follow up is quite short and we do not have time to have a transition phase immediately following implementation of the intervention. We will not be performing interim analyses and believe that it is very unlikely that anything in these analyses would give good grounds to change the duration of the steps. However the number and duration of steps will be reviewed by a project Evaluation Advisory Board, if needed, as dictated by operational and logistical issues. There are several laboratory IT systems in operation across the UK and the need for the eGFR graph system to work across multiple platforms may impact upon the project time-lines. Delays will be mitigated by over-recruitment and pre-allocation of intervention start time at the point of formal expression of interest.

The UK pathology laboratory environment is evolving. The Audit Commission called for pathology services to be re-organised in 1993, but changes have been slow to be implemented. “Hub and spoke” models were recommended in Lord Carter’s 2008 review of pathology services, where routine (including GP) work is consolidated into large hubs. This model offers both opportunities and threats. Consolidation of high volumes of GP samples into a single laboratory/laboratory cluster will allow a single site deployment of our intervention to reach far larger numbers of surgeries. The risks are that historic pathology data may not be transferred to new systems, preventing the retrospective charting of renal function, and that there may be pathology reorganisations at participating sites within the project lifespan.

Routinely collected data are readily available and inexpensive, but have inherent weaknesses when compared with trial data: they can be incomplete and subject to bias, and may not collected or reported uniformly across different sites. Although the unit of intervention in the project is the pathology laboratory, UK Renal Registry data are aggregated and reported at the level of the renal centre. If sites are recruited where not all laboratories serving a main renal centre implement eGFR graph reporting, it is theoretically possible to map late presenting patients to laboratories using Geographic Information Systems; however this process is imperfect and subject to significant inaccuracies as a result of boundary effects.

We recognise that generating enthusiasm for improvement activity within the current financial envelope in the National Health Service may be challenging. Although participating sites will be fully supported to deliver the intervention for one year, achieving sustainability beyond one year will require support from local commissioners, which we anticipate will be contingent on evidence of the cost-effectiveness (or potential cost-effectiveness) of the intervention. Exploring the drivers and barriers to lasting change will be a key output of the qualitative element of our evaluation. It should also be recognised that there is an irreducible minimum late presentation rate as a result of renal failure that develops acutely, as seen for example with myeloma kidney [24].

The provision of an eGFR graph surveillance service is a conceptually simple quality improvement intervention that we believe should benefit both patients and clinicians. By its nature it is well-suited to replication at other sites. Set against the annual cost of haemodialysis, the system has clear potential to be highly cost-effective. A demonstration that it is self-sustaining and effective across a range of contexts would create a powerful case for universal adoption of the service.

